### Measures

The baseline assesses all socio-demographic and trait constructs that are not expected to change due to the manipulation in the laboratory part of the study. In the laboratory momentary physiological, affective, self-evaluative, and relationship variables are assessed. The post-manipulation physiological assessments and self-reports repeat some of these momentary states to capture the effects of the four experimental conditions. An overview of the measurement points in time and instruments can be found in the SPIRIT chart in Table 3.

**Table 3 Tab3:**
[figure not shown]

[figure not shown]
SPIRIT schedule of enrolment, conditions, and assessments according to time points

### Socio-demographics

The following socio-demographic covariates are assessed: gender (male, female, diverse), age, partnership status (single, in an intimate relationship, married, separated, divorced, widowed), education level (German education levels, which can be categorized into three levels of the International Standard Classification of Education^1^ (ISCED, Unesco, 2011), employment status^2^, having children (yes/ no), private care work for children and/or adults and migration background (“Did you or your parents immigrate to Germany?” myself/ one parent/ both parents/ no).

### Self-report questionnaires

Self-report questionnaires are used at baseline, at arrival in the laboratory, directly pre-manipulation, directly post-manipulation and at the last measurements point shortly before debriefing. We describe every instrument shortly and indicate at which measurement points in time it is assessed in Table 3. More details on the measures can be found in the project material on OSF (https://osf.io/8spzw).

#### General life satisfaction short scale

The German version of the 1-item General Life Satisfaction Short Scale (L-1) is used to assess general life satisfaction on a scale ranging from 0 (not at all satisfied) to 10 (completely satisfied) [73].

#### Self-efficacy (to provide effective emotional support)

Following the study by Rossetto, Lannutti and Smith [74], participants self-report their perceived ability to provide emotional support (support-specific perceived self-efficacy) using a three-item efficacy scale adapted from a six-item scale used in previous support research [75]. The questionnaire was translated into German with minor changes in wording. Each item is rated on a 7-point Likert scale from 1 (strongly disagree) to 7 (strongly agree).

#### Social network questionnaire

The Social Network Questionnaire (SNQ) contains items that each represent a dimension of social relationships identified by Barrera [76]. Internal consistency have been described by Krause [77, 78]. The following three scales were selected from the SNQ (and translated to German) to assess the categories of interest for the survey: provided support, enacted support, and negative interactions. Items are scored on a 4-point Likert scale with 1 (never), 2 (once in a while), 3 (fairly often) and 4 (very often). The *provided support* scale measures the amount of emotional, tangible and informational support that respondents provided to others in the past 12 months. The items on the *enacted support* scale measure the estimated amount of emotional, tangible, and informational support received from others in the year prior to the survey. The scale for *negative interactions* measures how often others make excessive demands (1), are critical (2), interfere in the respondent's personal affairs (3) and take advantage of the respondent (4).

#### Need satisfaction through support provision

Based on the event-based scale to assess psychological needs satisfaction by certain events [79], a set of 9 items, translated into German, is used to measure the satisfaction of the basic needs of autonomy, competence and relatedness through the provision of social support with three items each. At baseline, the original instruction “During this event I felt…” was adapted to prompt participants to think of support situations “While providing support in the last month, I felt...”. Directly after the support manipulation in the laboratory, the questionnaire is used again with adapted instructions to measure basic need satisfaction during the experiment “During the task I just completed, I felt ...”. Participants respond on a scale from 1 (not at all) to 5 (very much).

#### Compassionate engagement and action scales

The subscale *Compassion for Others* from the Compassionate Engagement and Action Scales (CEAS; [80]) is used in a translated German version. The first part of the scale reflects compassionate engagement with others and consists of eight items (e.g., “I am motivated to deal with other people's distress and work with them when it occurs.”). The second part of the scale, measuring compassionate actions for others, consists of five items (e.g., “I take action and do things that are helpful to others.”). Each participant is asked to rate the frequency of the statement on a 10-point Likert scale from 1 (never) to 10 (always). The three reverse items were not included in the survey because the original study labeled these items as fillers and excluded them from the final analysis [80, 81].

#### Questionnaire of cognitive and affective empathy

*Cognitive and affective empathy* were measured using the Questionnaire of Cognitive and Affective Empathy (QCAE; [82]) in its German form (items from two previous German translations of the QCAE were used: [83, 84]). The *cognitive empathy* scale (19 items) includes subscales for *perspective taking* (e.g., “I am good at predicting what someone will do.”), and *online simulation* (e.g., “Before criticizing somebody, I try to imagine how I would feel if I was in their place.”). The *affective empathy* scale (12 items) includes subscales for *emotion contagion* (e.g., “It worries me when others are worrying and panicky.”), *proximal responsivity* (e.g., “I get very upset when I see someone cry.”), and *peripheral responsivity* (e.g., “I often get deeply involved with the feelings of a character in a film, play, or novel.”). Each item is rated on a 4-point Likert scale from 1 (strongly disagrees) to 4 (strongly agree) [82].

#### Communal orientation scale

The Communal Orientation Scale (COS; [85]) is a 14-item scale that assesses an individual's perception of the importance of others' needs and feelings in social relationships, as well as their belief in the obligation to assist others and promote their well-being (e.g., “When making a decision, I take other people's needs and feelings into account.”). Respondents answer each item on a 7-point Likert scale ranging from 1 (extremely uncharacteristic of me) to 7 (extremely characteristic of me).

#### Basic psychological need satisfaction

The shortened 12-item version of the Basic Psychological Need Satisfaction and Frustration Scale (BPNSFS; [86]) is used to assess *general basic psychological need satisfaction* in its validated German version [87]. The BPNSFS consists of three subscales: *autonomy*, *relatedness*, and *competence*, each containing satisfaction and frustration items (e.g., satisfaction with autonomy “I feel that my choices express my true self.”). The items are rated on a 5-point Likert scale ranging from 1 (strongly disagree) to 5 (strongly agree).

#### Big five inventory

 The BFI-10 [88] is a short 10-item version of the established Big Five Inventory (BFI; [89]) measuring the Big Five personality traits *extraversion*, *agreeableness*, *conscientiousness*, *neuroticism*, and *openness* with two items per dimension. The items are scored using a 5-point rating scale from 1 (strongly disagree) to 5 (strongly agree).

#### General self-efficacy scale

*General self-efficacy* is assessed with the German five-item short form of the General Self-Efficacy Scale (GSE; e.g., “It is easy for me to stick to my aims and accomplish my goals”; [90, 91]). Items are rated from 1 (strongly disagree) to 4 (strongly agree).

#### Brief rosenberg self-esteem scale

 The German five-item Brief Rosenberg Self-Esteem Scale (B-RSES; [92–94]) assesses *self-esteem* on a 7-point scale from 1 (strongly disagree) to 7 (strongly agree).

#### De Jong Gierveld loneliness scale

The short version of the De Jong Gierveld Loneliness Scale [95] includes *emotional loneliness*, characterized by perceived lack of intimacy in relationships, and *social loneliness*, characterized by perceived lack of quantity of social contact. Answers are rated from 1 (never) to 5 (always).

#### Self-rated health

*Self-rated health* (SHR), also known as self-perceived health, is a subjective evaluation of one's own health status and is assessed with the single item “How is your overall health status?”, which was translated into German. The answering options range from 1 (very good) to 5 (very bad). In comparison with other items for self-assessment of the health status, this item previously showed best construct validity [96].

#### Perceived stress scale

 The German short version of the Perceived Stress Scale (PSS-10; [97, 98]) is used to measure perceived *stress* in the last month before measurement. Cohen [98] found the PSS-10 to be valid and reliable and relatively superior to other versions of this questionnaire (PSS; PSS-4; [98]) in terms of internal consistency and factor structure. The questionnaire consists of ten items, each beginning with “In the last month, how often have you...” and has two subscales: *perceived helplessness* and *perceived self-efficacy*. The answers are given on a 5-point Likert scale ranging from 1 (never) to 5 (very often).

#### Patient health questionnaire for anxiety and depression

The German ultra-brief version of the Patient Health Questionnaire as a screening scale for *anxiety* and *depression* (PHQ-4; [99, 100]) combines the two core criteria for depressive disorders and the two core criteria for generalized anxiety disorder that have also been shown to be good screening items for panic, social anxiety, and posttraumatic stress disorders [101, 102]. The PHQ-4 begins with “Over the last 2 weeks, how often have you been bothered by the following problems?” and continues with different symptoms (e.g., “little interest or pleasure in doing things”). Responses are scored as 0 (not at all), 1 (several days), 2 (more than half the days), or 3 (nearly every day).

#### Relationship questionnaires

Three items assess the *dyadic relationship*, including the type of relationship (friendship/ romantic relationship), the relationship length (in months and years; based on [103]) and the frequency of contact (times per month; including phone calls).

As Fülöp et al. [104] suggested that the single-item Relationship Assessment Scale (RAS-1; [105], German version in [106]) can be used as a representative item for the overall construct of relationship satisfaction, it is used with an adapted wording in this study to measure overall satisfaction with the dyadic relationship “Overall, how satisfied are you with the relationship/ friendship with the person you are here with today?”. The item is rated on the original 5-point Likert scale from 1 (not at all satisfied) to 5 (very satisfied).

The *quality of the interaction* between the dyad partners on the day of the experiment is assessed with two items derived from prior studies on marital interactions [107, 108]. These two items capture the two dimensions of daily relationship quality: pleasure and tension. They were slightly adapted (e.g., “How tense/ enjoyable were your interactions with your partner person today?”). The response options range from 0 (not tense/ enjoyable at all) to 10 (as tense/ enjoyable as they could possibly be).

Following Väänänen et al. [109], the *perceived reciprocity in intimate relationships* and its components are measured according to the recommendations of Antonucci [110] and Hatfield et al. [111]. Focusing on the relationship of the dyads in this study, respondents are asked the following adapted question (translated to German) “In your relationship with this person, which of you gives or receives more support and help; how would you describe your relationship in this respect?” The following options to respond are provided: “I receive support and help more than I give.”, “I give support and help more than I receive.” or “I receive support and help as much as I give.”.

The 25-item Quality of Relationships Inventory (QRI; [112]) measures three aspects of specific relationships: social support, conflict, and depth, which are rated on a 4-point Likert scale, ranging from 1 (not at all) to 4 (very much). In line with the study interest to measure the *quality of the dyadic relationship*, only the items of the two dimensions social support (7 items, e.g., “To what extent could you turn to this person for advice about problems?”) and depth (6 items, e.g., “How significant is this relationship in your life?”) of the validated German QRI [113] are used. In the items, a minor change of the word “person” to “your partner person” was made to ensure that the respondents answered the items with regard to their dyad partner with whom they are undergoing the experiment.

#### Positive and negative affect schedule

*Positive and negative affective states* pre and post support manipulation are assessed with the short version of the Positive and Negative Affect Schedule (PANAS; [114, 115]). The short version of the PANAS consists of five adjectives each to measure positive and negative affect, respectively. The positive subscale describes an enthusiastic, active and alert state. The negative subscale describes the degree of negative tension caused by dejection, anger and anxiety [114, 115]. The German items were taken from the 20-item German adaptation by Breyer and Bluemke [116]. In order to capture the momentary affective state, participants are instructed to answer how they feel “in this moment” on a 5-point Likert scale from 1 (not at all) to 5 (extremely).

#### Spielberger state-trait anxiety inventory

The 10-item German Spielberger State-Trait Anxiety Inventory (STAI; [117, 118]) is used to assess current symptoms of anxiety, e.g., “I feel tense” or “I feel nervous”. Respondents are asked to choose between 1 (not at all) to 8 (very much).

#### Inclusion of other in the self scale

The Inclusion of Other in the Self Scale (IOS; [119]) is used to measure perceived *closeness* of the dyad partners pre and post manipulation. This single item is a pictorial measure of closeness, in which participants are asked to choose one of seven increasingly overlapping circles, each representing a greater degree of closeness. Instructions were translated into German.

#### State change questionnaire

 Based on the study by Løseth et al. [120], participants complete the State Change Questionnaire to capture manipulation-related changes in participants’ overall sense of subjective state. The two items assess whether participants feel better or worse after the manipulation and are answered on a visual sliding scale from 0 (not at all) to 100 (very much) [120]. The item time frame was adapted to “To what extent do you feel better/ worse than the last time you were asked about your mood?” and translated into German.

#### Evaluation of support provision

Based on Gallagher et al. [103], one item is used to capture the *provider’s own evaluation of support* (“How supportive do you think you were to the person being tested?”). Furthermore, two additional items were created in German language: “How helpful do you think you were to your partner person during the stress test?” and “How clearly recognizable was your support for your partner person during the stress test?” to measure the *provider’s own evaluations of recognizability of the provision of support*. Participants can respond from 1 (not at all) to 6 (extremely) plus one additional option 0 (“I have not written any support messages today”; for the observation condition).

#### Empathic reaction

Participants’ *empathic reaction* to their observation of their dyad partner's stress during the manipulation (“How well do the following adjectives describe how you felt emotionally when you observed your partner person's stress?”) is measured using six adjectives from the 23-item Emotional Response Questionnaire (ERQ; [121]). These adjectives of empathic concern (sympathetic, moved, compassionate, tender, warm and softhearted) can be split into the two components sympathy and tenderness [122, 123]. The items were translated into German and are rated on a scale from 1 (does not apply at all) to 5 (fully applies).

#### Motivation to help scale

Following Stehr [124], it is assessed whether participants experienced their support provision as autonomous or controlled with the German six-item version of the *Motivation to Help Scale* (original version by Weinstein & Ryan, [52]). Three items assess the extent to which participants experienced their support provision during the stress test as autonomous (e.g., “Because I thought it was important to act in this way.”) or controlled (e.g., “Because I’d feel like a bad person if I didn’t.”). Each item is rated on a scale from 1 (not at all true) to 5 (very true), while the control condition can choose “I did not write any support messages today”.

#### Prosocial behaviour

*Prosocial behaviour* is assessed with one item based on Batson et al.’s [125] prosocial behaviour experiments asking participants whether they would want to replace their partner for the second phase of the alleged six runs of the stress tests post-manipulation. Possible answers are “Yes, I would like to replace my partner person.” or “No, I would like to continue as the observer or supporter.”.

### Self-test

#### Multifaceted empathy test

Only at baseline, the cognitive and emotional aspects of empathic functioning are tested multidimensionally by the new version of the Multifaceted Empathy Test (version MET-core-2; [63, 64]). The MET-core-2 consists of a series of photographs, most of which depict individuals in emotionally charged situations. To assess cognitive empathy, subjects are asked to infer the mental states of the individuals shown in the photographs from a list of four options (higher numbers of correct answers are interpreted as higher cognitive empathy). To assess emotional empathy, subjects rate their emotional reaction in response to the pictures on a 9-point scale (emotional empathy as mean score of emotional reaction to the pictures). This test is not repeated as it will be used as a trait predictor for support provision measures.

### Covariates

#### Social desirability gamma scale

The German Social Desirability Gamma Scale (KSE-G; [126]) measures two aspects of the gamma factor of social desirability, the exaggeration of positive qualities and the minimization of negative qualities, with three items each. The 5-point rating scale ranges from 1 (doesn’t apply at all) to 5 (applies completely).

#### Initiative for study participation

As previous studies have shown that motivation has an impact on whether participants pay close attention to instructions and that motivation can affect study results [127, 128], a single item was developed to ask participants about their *initiative for study participation*: “Did you bring your partner person to this study or did your partner person bring you?”. The possible answers are: “I brought my partner person to this study”, “My partner person brought me to this study” or “We both became aware of the study and jointly agreed to take part in it”.

#### Preference for experimental task

The *preference for experimental task* (stress task vs. observer/ support provider) is assessed as a confounder with “Before starting the experiment, did you have a preference for either condition?” with the options “I was satisfied in my condition.”, “I did not care.”, and “I would have preferred to go through the stress test.”. We assume that the preference for one of the tasks of the experiment could affect the motivation to complete the experiment conscientiously (e.g., [127]).

### Manipulation checks

#### Stress experience

The participants' *individual perception of stress* during different phases of the test situation is assessed by four items developed for this study. These items are intended to show whether and to what extent participants are stressed by observing the stress and pain level of their dyad partner and at which phases of the experiment they feel stressed. Participants rate their perceived stress experience when observing their dyad partner's level of stress and pain during the stress test (1), when writing their support message to their dyad partner (2), when sending their support message to their dyad partner (3) and when receiving feedback via the chat on a scale (4; only in conditions in which feedback is received) on a visual sliding scale from 0 (not at all) to 100 (very much). Another response option is “I did not write any support messages today.” for participants in the control condition.

#### Perspective taking

*Perspective taking* is assessed as a manipulation check with three items from Pahl and Bauer [129] and the term “speaker” was replaced by “partner person”, “I imagined how my partner person is feeling right now.”, “I imagined how I would feel in the situation.”, and ”I put myself in my partner person's shoes.” with options on 9-point Likert scales ranging 1 (not at all) to 9 (very much).

#### Credibility

*Credibility* was assessed with two items on a semantic differential answering format “The experimental situation made the following impression on me…” from 1 (artificial) to 10 (real), and from 1 (incredible) to 10 (credible) and one item to assess whether participants in the support provision conditions perceived thankfulness from the alleged recipients “My partner person was grateful for my support during the stress test” with answers ranging from 1 (not at all) to 10 (very much), and one option for the control group “I did not write any support messages today.”.

### Physiological measures

During the laboratory experiment, three psychological parameters (cortisol, heart rate and heart rate variability, blood pressure) are taken as indicators of stress reactivity (e.g., [130–132]). All assessment points can be found in Table 3.

#### Saliva cortisol

 Saliva cortisol secretion, as a physiological response to stress, involves the release of a glucocorticoid hormone in humans that reflects the adaptation of the hypothalamic-pituitary-adrenal (HPA) axis to stressors [68]. The assessment of cortisol levels in saliva is a reliable, repeatable, safe, and non-invasive method for assessing stress reactions [131, 133, 134]. Saliva cortisol is assessed by means of five non-invasive saliva samples during the laboratory phase of the study at baseline, pre-manipulation, directly post-manipulation (0 minutes), 10 minutes follow-up, 30 minutes follow-up and 40 minutes follow-up (see Fig. 3; use of Salivette® Cortisol, Sarstedt).

#### Heart rate and heart rate variability

During the manipulation phase, the heart rate (HR) and heart rate variability (HRV) is recorded using the Polar H10 chest belt (Polar Electro UK Ltd). Data are stored via Bluetooth with the Kubios software [135] on mobile devices and the Kubios software is used on laptops for data analysis.

#### Blood pressure

Systolic and diastolic blood pressure is assessed using an upper-arm blood pressure monitor (Beurer BM58) during the laboratory phase of the study at baseline (twice, directly at arrival and after the acclimatization phase, about 30 min after arrival), pre-manipulation, directly post-manipulation (0 minutes) and 10 minutes follow-up.

### Planned analyses

Analyses of variance and linear mixed models between conditions and pre- and post-assessments will be performed on self-reported self-evaluative and affective as well as, physiological data and relationship variables. Of particular interest will be changes in positive and negative affect and ratings of competence and relatedness depending on the condition.

Data from participants who do not complete the full manipulation (that drop-out before the post-assessment) or show suspicion (e.g., enter trick questions into the chat boxes in order to check, whether they chat with their partners) will be analysed separately in per protocol and intention-to-treat analyses. No outliers are expected in the self-report data. In the event that participants fail to comply with the inclusion criteria for cortisol assessment (no strenuous exercise, food, alcohol, tooth brushing, smoking, caffeine, or cortisol affecting medication prior to the experiment), their cortisol data may have to be excluded post-hoc. Women who take oral contraceptives are included in the sample. For physiological data (cortisol, heart rate, heart rate variability, blood pressure) we consider truncation at 2 SD from the sample mean if outliers occur. Missing data will be handled via Full Information Maximum Likelihood (FIML).

In exploratory qualitative content analyses, we will investigate type and amount of support messages written into the computer chat boxes by participants in the three support provision conditions.

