The new experimental paradigm was developed to better understand under which preconditions of psychological needs satisfaction (self-determination theory; [51]) social support provision is beneficial for physiological, affective, self-evaluative, and relationship outcomes in providers. We propose that for positive effects to emerge, providers need to support their dyadic partner autonomously (this condition is not manipulated but present in all support conditions), and to build a sense of *competence* and a sense of *relatedness* in providers. Through the experimental manipulation of *competence* and *relatedness*, the causal conditions under which support giving is beneficial for the provider can be extracted from possible confounding variables, such as differences at baseline (e.g., personality, health) and from possible reversed effects (individuals with greater resources providing more support).

The primary objective of this study is to examine whether support providers who receive feedback on the positive impact of their support on the recipient (competence) and on their dyadic partners' appreciation of the support (relatedness) will demonstrate less pronounced increases and/or faster decreases in their physiological stress reactions, more positive affect, more positive self-evaluative and possibly also relationship evaluative reactions than providers who do not receive such feedback. To achieve this, four conditions will be randomized: 1) No support provision (observation condition = control), 2) autonomous support provision without feedback (autonomous support provision only condition), 3) autonomous support provision with feedback on competence (autonomous support provision + competence condition), and 4) autonomous support provision with feedback on relatedness (autonomous support provision + relatedness condition). The following main hypotheses will be tested:

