### Sample size calculation

Meta-analyses summarizing effects of experimental manipulations of prosocial behaviour on well-being resulted in small- to medium-pooled effects sizes from Cohen’s d = .28 [33] to Pearson’s r = .32 (corresponding to a Cohen’s d = .68; 43). Whereas these effect sizes represent support provision vs. no support provision, we are particularly interested in manipulating and comparing the effects of different conditions under which support is provided. Therefore, we base our power analyses on a small n^2^ of 0.02 for the interaction term of time*condition (Cohen, 1992; effect size f = 0.17). We deem a power of 95% desirable to detect effects not only between the ‘support’ to ‘no support’ group, but also between the groups that provide support under different conditions. With 4 between- and 2 within-subject factors entered into a repeated measures ANOVA, G*power estimates a total *N* = 216 (54 per group) to result in a 95% chance to reject the null hypothesis of no significant interaction term [66]. To allow for attrition due to failed manipulation (e.g., participants provide no support despite randomized to chosen support groups), we plan to recruit 250 participants randomized to four groups (125 dyads).

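### The planned pre/post time x condition test is a change-score comparison; adjusting for the pre-manipulation value would be more precise, and no contrast is tied to faster decreases

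*Protocol article*

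**What the plan says.** Protocol article, Planned analyses: "Analyses of variance and linear mixed models between conditions and pre- and post-assessments will be performed" on self-reported, physiological and relationship data. Changes in affect are singled out as of particular interest, and missing values are to be handled by FIML. The Socio-demographics and Covariates sections name several covariates; the pre-manipulation value of the outcome is not among them.

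Sample size calculation: "we base our power analyses on a small n^2^ of 0.02 for the interaction term of time*condition", printed with "effect size f = 0.17". The layout is "With 4 between- and 2 within-subject factors entered into a repeated measures ANOVA", read here as four groups and two measurements. The stated result is a total of "216 (54 per group) to result in a 95% chance to reject the null hypothesis of no significant interaction term", with 250 to be recruited.

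Objectives of study 2: providers who receive feedback are expected to show "less pronounced increases and/or faster decreases in their physiological stress reactions".

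Saliva cortisol: "five non-invasive saliva samples during the laboratory phase of the study at baseline, pre-manipulation, directly post-manipulation (0 minutes), 10 minutes follow-up, 30 minutes follow-up", followed by a further sample at 40 minutes. Blood pressure: readings before the manipulation, directly after it and 10 minutes later, besides two at baseline.

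**The concern.** There are two linked issues and one separate slip.

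1. **Precision.** A two-point time x condition interaction weights the pre-manipulation value with a coefficient of exactly one. Adjustment lets the data set that coefficient, and under randomisation this costs nothing in bias. If the pre-post correlation is lower than the sample size needs, the change-score test loses power quickly and the adjusted test much less.
2. **Recovery.** The primary objective covers both a smaller rise and a faster fall. The schedule follows cortisol to 40 minutes and blood pressure to 10 minutes, but the analysis section does not say which comparison would show a faster fall. The two-measurement power model does not represent one.
3. **Sample count.** The cortisol section gives a count of samples that differs from its own list of time points.

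**Working it through.** **Inputs.** From Sample size calculation: four groups, two measurements, eta-squared 0.02, target power 95%, N = 216. Assumed because not stated: alpha = 0.05, and pre-post correlation rho = 0.5, chosen because it reproduces N = 216. Equal variances at both times. As in the repeated-measures formula, participants are treated as independent.

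**Step 1: reproduce the plan's figure.**
- f-squared = 0.02/0.98 = 0.0204, so f = 0.143.
- Noncentrality lambda = f-squared x N x m/(1 - rho) = 0.0204 x 216 x 2/0.5 = 17.63, with 3 and 212 degrees of freedom.
- Power = 95.2%. The smallest N with equal groups is 216, which matches.
- The printed f = 0.17 does not follow from eta-squared 0.02. With rho = 0.5 it gives N = 156; with rho = 0.3 it gives 212, close to 216. The document therefore does not settle rho.

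**Step 2: compare variances** (per person, in units of the single-measurement variance).
- Change score: 2(1 - rho).
- Adjusted for the pre-manipulation value: 1 - rho-squared.
- Ratio: (1 - rho-squared)/(2(1 - rho)) = (1 + rho)/2, never above 1.
- At rho = 0.5 this is 0.75/1.00 = 0.75. A simulation with 54 per group and 20,000 runs gave 0.758.

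**Step 3: convert to power.** Hold the raw condition differences at the size implied by Step 1. Then lambda = 4 x f-squared x N/variance, and 4 x 0.0204 x 216 = 17.63 is divided by each variance. The adjusted test has 211 error degrees of freedom.

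| rho | Variance, change | Variance, adjusted | Reduction | lambda, change | lambda, adjusted | Power at 216, change | Power at 216, adjusted | N for 95%, change | N for 95%, adjusted |
|---|---|---|---|---|---|---|---|---|---|
| 0.3 | 1.40 | 0.91 | 35% | 12.60 | 19.38 | 85.2% | 96.8% | 300 | 196 |
| 0.5 | 1.00 | 0.75 | 25% | 17.63 | 23.51 | 95.2% | 98.9% | 216 | 164 |
| 0.7 | 0.60 | 0.51 | 15% | 29.39 | 34.57 | 99.8% | 99.9% (rounded down) | 132 | 112 |

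Over a wider range the reduction is 40% at rho = 0.2 and 5% at rho = 0.9. These figures concern one pre and one post measurement.

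**Step 4: set objective against schedule.** Post-manipulation cortisol is due at 0, 10, 30 and 40 minutes, and blood pressure at 0 and 10 minutes. A model with one pre and one post value has no slope after the manipulation. The wording of Planned analyses allows a mixed model holding all these samples, but names no contrast for a faster fall.

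**Step 5: count the saliva samples.** Baseline, pre-manipulation, 0, 10, 30 and 40 minutes make six. The text says five.

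**The case against.** The strongest reply is that nothing here is wrong. Under randomisation the change-score comparison is unbiased, and on the assumptions that reproduce N = 216 it meets its 95% target, with 250 to be recruited. A condensed article may leave covariates and contrasts to a fuller plan, and the planned mixed models do not rule out adjustment. A mixed model with the pre-manipulation value as an outcome and a common baseline mean would recover essentially the same efficiency. All of that stands. It limits the point to an improvement in a stated method.

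Three stronger readings are tempting and are not supported:

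- **That faster decreases go untested.** The two-measurement layout appears in the sample size calculation. Planned analyses refers to mixed models and to post-assessments in the plural, which can hold every post sample. What is absent is a contrast tied to that part of the objective.
- **That 25% is the plan's own figure.** No correlation is stated. The value 0.5 is inferred from N = 216 and eta-squared 0.02, and the printed f = 0.17 points elsewhere.
- **That a power gain for H5 can be quoted.** It would require carrying the four-group f over to a two-arm contrast, which the document does not do.

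Two limits on the remedy also stand. H1 asks whether responses change in all conditions, so it needs the pre-manipulation value as an outcome. Heart rate and its variability are described only as recorded during the manipulation, so the figures do not carry over to them directly.

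**Conclusion.** The point holds as a matter of efficiency and of linking the analysis to the objective. The stated and powered test compares change scores, and the protocol names no adjustment for a pre-manipulation value that it schedules. Adjusting multiplies the variance by (1 + rho)/2: a 25% reduction at rho = 0.5, 35% at 0.3, 15% at 0.7. The practical gain depends on the true correlation. At 0.5 the omnibus test already meets its target and moves from about 95% to 99%. At 0.3, with the same raw differences, it would fall to about 85%, against about 97% with adjustment. These figures assume alpha 0.05, equal variances, independent participants and one post measurement. The missing link to faster decreases is a gap in wording, and the saliva count is a separate inconsistency that does not bear on the precision argument.

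**What to change.** 1. For H3 to H5, on outcomes measured both before and after the manipulation, state that the between-condition comparison is adjusted for the pre-manipulation value, either as a covariate or through a common baseline mean across conditions in the mixed model.
2. Keep the pre-to-post time effect, with the pre-manipulation value as an outcome, for H1.
3. For cortisol (0, 10, 30 and 40 minutes) and blood pressure (0 and 10 minutes), state that all post samples enter the model, and name the condition x time contrast over them as the test of faster decreases. An average over the post samples alone would not separate a faster fall from a smaller rise.
4. State the pre-post correlation behind N = 216 and reconcile it with the printed eta-squared and f.
5. Reconcile the stated five saliva samples with the six time points listed.

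The cost is analysis wording and code. The measurements are already scheduled, and the article reports that data collection is still ongoing, so the change can be recorded before analysis.
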